### Study procedures

Research associates and/or research team members will screen for eligible patients using a screening form based on the inclusion/exclusion criteria mentioned above. Results will be analyzed at two stages: first, with the results of the questionnaires administered as part of the initial visit, and second, after concluding the 3–12 month follow-up survey. The consent, educational video, and questionnaire will all be conducted while the patient is in the waiting room, after the clinician (physician or advanced practice provider) has completed the initial patient encounter, or after the provider contact has been completed.

The patients will fill out the composite questionnaire. This questionnaire is designed with the following criteria: prioritize using validated tools capable of self-administration. The Readiness-to-Change questionnaire evaluates patient readiness to implement ten lifestyle behaviors based on a 5-point rating scale. A rating of 5 represents having no interest in the suggested lifestyle change, which is consistent with the precontemplation stage of the transtheoretical model (TTM). A rating of 4 means an interest in implementing the lifestyle change in the next few months (contemplation stage of the TTM). A rating of 3 represents having the plan to implement the lifestyle change within the next month (preparation stage of the TTM). A rating of 2 represents having already started the lifestyle change within the past few months (action stage of TTM). A rating of 1 means having maintained lifestyle behavior changes for over 6 months (maintenance stage of TTM). The Confidence-to-Change questionnaire evaluates patient confidence in implementing the same lifestyle behaviors as the Readiness-to-Change questionnaire. However, the Confidence-to-Change questionnaire is based on a 3-point rating scale. Ratings are as follows: 3-very confident, 2-somewhat confident, and 1-not very confident [12]. The Confidence-to-Change questionnaire addresses any barriers or hesitancy that may impact patient confidence in implementing better lifestyle behaviors. Additional questions will include measures of satisfaction taken from the HCAHPS, specifically addressing their practitioner and visit (S2 Appendix B).

Sometime after the visit (target: 3–12 months later), they will receive a phone follow-up call, asking them if they have adopted any lifestyle changes since watching the video, among other inquiries (S3 Appendix C). We will use patients’ responses at this later stage (follow-up phase) to help determine how sustainable the preventive education intervention has been.

Randomized patients who participate in the study will receive the video intervention. In a previous pilot study, we investigated the impact of a simple instructional video on patients’ willingness to change in the emergency department setting [13]. The initial intervention was passive, requiring subjects to watch a video without interaction. The current study evaluates the practicality and impact of bringing a brief *interactive* educational video intervention to patients attending the primary care clinic visit.

All patients, including those randomized to “no video learning,” will be asked to complete a questionnaire. The questions will be administered orally or self-administered for those willing to participate using the tablet interface. Responses will be recorded using REDCap electronic data capture software and the related platform.

A sample size of approximately 350 was chosen based on feasibility and the expectation of sufficient power to detect moderate differences in readiness and confidence scores, guided by prior pilot study results. Due to the minimal risks in this study, a data monitoring committee is not considered necessary. An interim analysis will be conducted after 200 patients have been enrolled. It is anticipated that the total data collection will take six months. For those patients who agree to receive a call-back, contact will be attempted during the 3–12-month follow-up period. A research associate, a resident, or an attending physician will complete the follow-up by telephone or email correspondence with the subject. Up to 3 follow-up attempts will be made. Available follow-up data from the interactive electronic health record (EHR) will be obtained on all patients. The estimated time to view and interact with the video is approximately 10–15 minutes. The time required for responses to the survey component is estimated at 10–12 minutes.

The EHR will be used to determine several variables: age, race, ethnicity, sex and gender, BMI, and the Charlson Comorbidity Index (CCI). Michigan Data Analytics will assist in generating the patient’s CCI from ICD-10 codes, and other information from the patient's medical record. Information from the patient’s chart will only be obtained from those who provide informed consent.

The research team training will include informed consent, knowledge of the inclusion and exclusion criteria, using the EPIC EHR, and practice administering the study. The study will be performed using a convenience sample when team members are available to facilitate the study procedures.

Upon completion of the study, the results will be analyzed and presented at regional and national scientific meetings and for publication. The protocol was submitted for publication prior to the initiation of the trial. Authorship of the resulting publication will follow the guidelines of the International Committee of Medical Journal Editors (ICMJE). No professional writers will be used for publication. No individual patient identifiers will be revealed during the abstract presentation or publication of the results. The data will be maintained in a password-protected electronic file on a hospital server using REDCap, a secure electronic data capture system.

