### Study hypotheses

We hypothesize that patients receiving the interactive video intervention will exhibit greater readiness and confidence to change lifestyle behaviors compared to patients in the control group, as measured immediately post-intervention.

Null hypothesis (H₀): There is no difference in readiness and confidence to change lifestyle behaviors between the intervention group and the control group.

Alternative hypothesis (H₁): The intervention group will demonstrate significantly greater readiness and confidence to change lifestyle behaviors than the control group.

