### Participant enrollment and screening

Adult patients aged 18–80 will be recruited by a study team member or a research associate before their appointment or upon arrival at an Academic Internal Medicine ambulatory clinic. Please see the flow diagram for the randomization process and the table for the study process (Fig 1 and Table 1).

**Table 1 pone.0322244.t001:** Schedule of enrollment, interventions, and assessments.

	STUDY PERIOD				
	Enrollment	Allocation	Post-allocation		Close-out
TIMEPOINT	-t_1_	0	t_1_ (time 0)	t_2_ (3–12 months)	t_x_
ENROLLMENT:					
Eligibility Screen	X				
Informed Consent	X				
HIPAA Waiver	X				
Randomization/Allocation		X			
INTERVENTIONS:					
Watch Video			X		
Standard-of-care			X		
ASSESSMENTS:					
Baseline Assessment*	X				
Primary Outcomes**			X		X
Secondary Outcomes***			X		X
Follow-up Survey				X	X

*Sociodemographic, clinical, and lifestyle characteristics.

**Readiness/Confidence to Change questionnaires.

***Satisfaction with the primary care clinic visit and others.

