Outcomes collected at the clinic visit (e.g., readiness to change and confidence to change) will be compared between intervention and control groups using ordinal logistic regression, appropriate for ordinal outcome variables. As these measurements are taken after randomization and intervention (where applicable), no pre-intervention baseline measures will be available.

Follow-up outcomes, including receipt of additional care, adoption of lifestyle changes, and overall well-being, are recorded as binary or categorical variables (e.g., Yes/No/Don’t Know) and will be analyzed using logistic regression models. Clinic visit scores may be included as covariates to assess their association with follow-up outcomes.

A complete-case approach will be used for all primary and secondary outcome analyses. Differences in loss to follow-up between study arms will be reported, and characteristics of completers and non-completers will be compared to assess potential attrition bias. Multiple imputation is not planned due to the structure of data collection involving a single follow-up time point.

Separate regression models will be used to analyze outcomes collected at the clinic visit and follow-up. Given the design of the study, which includes a single post-intervention follow-up and no pre-intervention baseline, repeated measures modeling will not be used in the primary analysis. Secondary analyses may include generalized estimating equations or other repeated measures approaches to assess the consistency of findings.

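### The two best readiness ratings record behaviour begun before the visit, so the readiness half of the primary outcome is diluted, by an amount that depends on the unstated share already acting and on scoring

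*Protocol article*

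**What the plan says.** All places are in the Protocol article.

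- **Scale (Study procedures).** Ten behaviours are each rated 1 to 5, with 5 the least ready. Ratings 5, 4 and 3 concern intention: no interest, interest over the coming months, a plan for the next month. The other two concern the past: "A rating of 2 represents having already started the lifestyle change within the past few months (action stage of TTM"), and "A rating of 1 means having maintained lifestyle behavior changes for over 6 months". The companion Confidence scale has three points and does not refer to past behaviour.
- **Timing (Participant enrollment and screening; Study procedures).** The questionnaire follows the video in the same visit. The video takes about 10–15 minutes.
- **Population (Eligibility).** Adults aged 18–80 are eligible whatever they already do about diet, exercise, sleep or smoking.
- **Analysis (Statistical methods; Abstract).** Readiness and Confidence are compared between arms by ordinal logistic regression. The named covariates are comorbidity index, age, sex and gender, plus prespecified predictors that are not listed. The section adds that "no pre-intervention baseline measures will be available".
- **Enrolment data (Table 1 footnote).** A baseline assessment before randomization covers "Sociodemographic, clinical, and lifestyle characteristics".
- **Sample size (Study procedures).** "A sample size of approximately 350 was chosen based on feasibility" and on "the expectation of sufficient power to detect moderate differences in readiness and confidence scores, guided by prior pilot study results".

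**The concern.** The hypothesis is that "The intervention group will demonstrate significantly greater readiness and confidence to change lifestyle behaviors than the control group". On the readiness scale, two of the five levels cannot be reached through a video seen minutes earlier, if patients answer truthfully. Patients already at those levels add spread but no information about the effect.

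Ordinal logistic regression in its usual proportional-odds form assumes one odds ratio at every cut of the scale. Here it is 1 at the two cuts that involve past behaviour and differs from 1 at the other two. The fitted common value is pulled toward 1.

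At stake are the power of the readiness comparison and the reading of a null readiness result, which could reflect an ineffective video or a scale with little room to move. An analysis plan written later cannot recover a pre-video measure that was never taken.

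**Working it through.** **1. The plan's own figure.** No effect size, SD, alpha, power or pilot result is given, so 350 cannot be derived. As a plausibility check, assume 1:1 allocation and two-sided 0.05. For 80% power, n per arm = 2(1.96 + 0.84)²/d². At d = 0.30 this is 15.7/0.09 ≈ 175. With 175 per arm, power is 91% at d = 0.35 and 99.7% at d = 0.5. The number is adequate if the effect can act across the whole scale.

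**2. Single item: inputs.**
- n = 175 per arm.
- Share f already in ratings 1–2: not in the documents, varied from 0 to 60%.
- Control split of the rest over ratings 5/4/3: 40/40/20. The Introduction gives this spread for current smokers only.
- Odds ratio among those not yet acting: 2 (assumed).

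**3. Treated split.** P(5): odds 0.4/0.6 = 0.667, halved to 0.333, gives 0.250. P(5 or 4): odds 0.8/0.2 = 4, halved to 2, gives 0.667. The split is 25.0/41.7/33.3.

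**4. Effect on the rank scale.** Let θ = P(treated patient better) + ½P(tie). Among those not acting, θ₀ = 0.250×0.2 + 0.417×0.6 + 0.333×0.9 = 0.600. Pairs in which either patient already acts contribute no net difference, so θ − 0.5 = (1 − f)² × 0.100. Power ≈ Φ((θ − 0.5)/SE − 1.96).

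SE at f = 0: the variance of the pairwise score is 0.430 − 0.360 = 0.0700 over treated patients and 0.4292 − 0.3600 = 0.0692 over controls. Then √((0.0700 + 0.0692)/175) = 0.0282.

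| f | θ − 0.5 | SE | Power |
|---|---|---|---|
| 0 | 0.100 | 0.0282 | 94% |
| 20% | 0.064 | 0.0297 | 58% |
| 30% | 0.049 | 0.0301 | 37% |
| 40% | 0.036 | 0.0302 | 22% |
| 50% | 0.025 | 0.0302 | 13% |
| 60% | 0.016 | 0.0299 | 8% |

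A separate run of the same case gave 93, 56, 37, 22, 12 and 8%. Simulated proportional-odds fits agree: power 59, 24 and 10% at f = 20, 40 and 60%, with fitted odds ratios of 1.55, 1.26 and 1.12.

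**5. Fit of one odds ratio, at f = 30%.** Cumulative control probabilities at ratings 5 and 5–4 are 0.28 and 0.56; treated, 0.175 and 0.467. The cut-specific odds ratios are (0.28/0.72)/(0.175/0.825) = 1.83 and (0.56/0.44)/(0.467/0.533) = 1.45. They are 1.00 at the remaining two cuts.

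**6. Sensitivity to the odds ratio.** At f = 0, 20, 30, 40 and 50%, an odds ratio of 2.5 gives 99.7, 81, 57, 35 and 19%; 1.75 gives 81, 41, 26, 16 and 10%. An even split over ratings 3–5 changes these by about a point at most.

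**7. Ten-item total.** Simulations with odds ratio 2 for behaviours not yet practised, over a range of within-person correlation and clustering, give roughly 83–100%, 67–96% and 41–70% at f = 20, 30 and 50%. The ends move with the range chosen; one wider set gave 38–78% at 50%. A smaller effect costs more: a latent shift of 0.3 SD (correlation 0.3) gives 99% at f = 0, 72% at 20%, 34% at 40% and 24% at 50%.

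**8. With the fix.** Adjusting a ten-item total for the number of behaviours already practised restores power to about 97–100% at odds ratio 2. Restricting a single item to those not acting at enrolment gives 89% at f = 20% and 78% at f = 40%.

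**9. Under the null.** If the video does nothing, θ = 0.5 at every f. There is no false-positive bias.

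**The case against.** - **The size is assumed.** No section gives the share already acting, and the 40/40/20 split is for smokers. This stands. The figures are a range, not a property of the trial.
- **One rating per patient is the worst case.** There are ten items, and a total loses much less. This stands for moderate effects, but a total still loses substantially when half the behaviours are already practised or the effect is small.
- **Confidence is untouched.** This stands. It is the other part of the primary outcome, and this mechanism does not reach it.
- **Existing data may suffice.** Lifestyle characteristics are taken at enrolment, smoking status comes from the health record, and the unlisted predictors might include prior behaviour. This stands in part: nothing stated shows a measure for each of the ten behaviours, and readiness itself has no baseline.
- **The analysis could be confined to post-video ratings 3–5, or non-proportional odds allowed.** Modelling the odds is properly left to an analysis plan. Selecting on the post-video rating is not a safe substitute: the video may change how patients classify themselves, and the rating is the outcome.

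A reader might infer that most of the trial's power is lost, or that any null result could not be interpreted. The documents support neither. On a single item more than half the power goes only from a share of about 30% (odds ratio 2) or 40% (2.5), a total holds up better, and Confidence remains interpretable.

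**Conclusion.** The concern holds for readiness only. By the protocol's own definitions, ratings 1 and 2 lie beyond the truthful reach of a video watched minutes earlier, and nothing stated in the design separates patients already there from those who can respond. The readiness comparison is diluted and a common odds ratio describes it poorly, though it remains valid under the null.

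The loss ranges from slight (a ten-item total with few already acting) to severe (a single item with 30% or more already acting). It rests on the assumed odds ratio, the smokers' split, 175 per arm, two-sided 0.05 and an unknown share already acting. The stated "the expectation of sufficient power to detect moderate differences in readiness and confidence scores" is therefore not supported for readiness without qualification. This is a cheap improvement to make before enrolment, not a flaw that invalidates the trial.

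**What to change.** 1. In Table 1's pre-randomization baseline assessment, add one yes/no item per behaviour asking whether the patient already does it (for smoking, whether a current smoker).
2. Adjust the primary readiness analysis for it: the number already practised for a total score, the item itself for a single behaviour. Keep all randomized patients.
3. Prespecify, as a supporting analysis, readiness among behaviours not practised at enrolment. Never select on the post-video rating.
4. In Statistical methods, revise the statement that no baseline will exist. In Study procedures, qualify the power expectation for readiness by stating the scoring and the assumed share already acting.

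**Cost:** about 1–2 minutes at enrolment and a small amendment. The items may slightly prime patients in both arms, which could narrow the contrast a little.

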**Fig 1 pone.0322244.g001:**
[figure not shown]
Flowchart for the study process. Note that all videos will use the interactive format. Patients will not be video recorded.

The randomization module within Research Electronic Data Capture (REDCap) will be used to allocate the video intervention. Those randomized for the intervention will be asked if they are interested and willing to watch a video about the clinic visit and their health. Those who agree to watch will then interact with a video featuring lifestyle changes relating to diet, exercise, sleeping, and smoking and why they are important for one’s overall health. The media is interactive because it contains questions for the user to answer at different points within the video sequence. The control group will not watch the video.

The study includes two surveys: the first will be administered in the clinic, and the second will be a follow-up survey administered upon phone contact with consenting patients. Target follow-up is planned for 3–12 months following the initial visit.

Whether receiving the video intervention or not, all participants will have provided verbal consent to answer the questionnaires (see the included script at the heading of the initial survey instrument within S2 Appendix B). They will then fill out the questionnaire at the end of the video either alone, with the assistance of an accompanying relative, or with the assistance of a research team member to determine their stage of the transtheoretical model. A study identification number will be placed on the completed survey. The ID number and the patient’s identifying information will be noted in REDCap. Any patient who declines to participate will not have their patient health information (PHI) included in the study. The REDCap file containing the patients’ personally identifiable information will be kept on password-protected servers using the institution’s REDCap.

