### Statistical methods

The study team members will collect demographic data upon registration to the patient’s clinic. Patients from ages 18–80 will be included in the study. After informed consent, patients will be randomized to either the intervention or the control arm of the study. Only the interventional arm will interact with the video using a provided computer tablet which focuses on lifestyle preventive education. Control patients will not receive a video and will go directly to the follow-up questionnaire. Hence, both groups will receive the follow-up survey from research team members.

The Demographic data includes age, sex, gender, race, and insurance status. The patient’s BMI, Charlson Comorbidity Index, smoking status, responses to the social influences of health questionnaires, phone number, and frequency of ED visits will be documented from the patient’s EHR. Their zip code will also be collected for geographic and socioeconomic status analysis (S1 Appendix A).

The study’s primary outcome is the readiness and confidence to change scores as a function of video exposure, measured on a continuous “readiness ruler.” [14].

Secondary outcomes will include readiness to change in specific domains, including exercise, smoking, diet, sleep hygiene, living an overall healthy lifestyle, satisfaction with the hospital, and satisfaction with the practitioner, dichotomized between those who watched the video and those who did not. Part of this data will be obtained directly from the patient’s medical record (S1 Appendix A).

We will collaborate with Michigan Data Analytics, which will provide large-scale data abstraction to assist with obtaining the Charlson Comorbidity Index (CCI) for participating subjects. The remaining data will be collected using the Readiness-to-Change and Confidence-to-Change Lifestyle Questionnaires, the Pittsburgh Sleep Quality Index (PSQI), and U.S. Governmental HCAHPS Patient Satisfaction Survey.

Descriptive statistics will be used to summarize baseline characteristics by study arm, including means and standard deviations for continuous variables and proportions for categorical variables. All analyses will follow the intention-to-treat principle.

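### The 3–12-month lifestyle-change question is described as counting from watching the video, which control patients and video-arm decliners never did

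*Protocol article*

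**What the plan says.** - **The question.** Protocol article, Study procedures: the follow-up call is described as "asking them if they have adopted any lifestyle changes since watching the video, among other inquiries", with a pointer to S3 Appendix C.
- **Who is called.** The same section says "For those patients who agree to receive a call-back, contact will be attempted during the 3–12-month follow-up period". Agreement to be called is the only condition, and arm is not mentioned. Participant enrollment and screening likewise speaks of consenting patients, and times the follow-up from the initial visit.
- **Controls.** Participant enrollment and screening: "The control group will not watch the video". Statistical methods repeats it: "Control patients will not receive a video".
- **Video-arm decliners.** Participant enrollment and screening says that patients randomized to the intervention are asked whether they are willing to watch, and only those who agree do so. Statistical methods puts all analyses under intention to treat, so decliners stay in the video arm.
- **The analysis.** Statistical methods: "adoption of lifestyle changes, and overall well-being, are recorded as binary or categorical variables (e.g., Yes/No/Don’t Know", and these follow-up outcomes go into logistic regression. Loss to follow-up is to be reported by arm.
- **A neutral description of the same survey.** The Outcomes paragraph of the Abstract says only that it covers self-reported lifestyle changes and new diagnoses.

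**The concern.** A between-arm comparison of a self-reported outcome needs both arms to be asked the same thing over the same period. A question that counts from watching the video gives viewers a start date and gives everyone else none. A control might answer No, answer Don't Know, or answer for whatever period the caller suggests. None of these measures what a viewer's answer measures. A video-arm patient who declined the video has the same difficulty, so the question follows actual viewing and not randomization.

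Study procedures says that these answers will help show how sustainable the education has been. The outcome is self-reported in an open trial, so a common time anchor is one of the few protections available. Answers collected with the wrong anchor cannot be repaired later.

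**Working it through.** The documents give no figure to reproduce here: no adoption rate, and no alpha, power or effect size behind the sample of about 350. The check is therefore a comparison of the text, followed by illustrations on assumed inputs.

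**1. The text side by side**

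| Patient group | Called at 3–12 months? | Watched the video? | Does a since-the-video anchor apply? |
|---|---|---|---|
| Video arm, watched | If they agree to a call | Yes | Yes |
| Video arm, declined | If they agree to a call | No | No |
| Control arm | If they agree to a call | No | No |

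One sentence in Statistical methods, "Hence, both groups will receive the follow-up survey from research team members", seems to settle that both arms get the survey. I do not rely on it. The sentence before it, "Control patients will not receive a video and will go directly to the follow-up questionnaire", uses the term follow-up for the in-clinic questionnaire. That the call covers both arms rests on the call-back sentence and on attrition being reported by arm.

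**2. How the bias depends on the answers**

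Assume that 40% truly adopt a change in both arms, that video-arm answers are correct, and that a share m of the affected controls misanswers. The last column is the apparent benefit of the video, 40% minus the observed control rate.

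| Control behaviour | Observed control rate | m = 10%, 20%, 30% | Apparent benefit (points) |
|---|---|---|---|
| Adopters say No, or Don't Know counted as No | 0.40(1−m) | 36%, 32%, 28% | +4, +8, +12 |
| Adopters say Don't Know and are dropped | 0.40(1−m)/(1−0.40m) | 37.5%, 34.8%, 31.8% | +2.5, +5.2, +8.2 |
| Adopters and non-adopters alike say Don't Know and are dropped | 0.40(1−m)/(1−m) | 40%, 40%, 40% | 0, 0, 0 |
| Only non-adopters say Don't Know and are dropped | 0.40/(1−0.60m) | 42.6%, 45.5%, 48.8% | −2.6, −5.5, −8.8 |

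Neither the size nor the sign is fixed until one knows who misanswers and how Don't Know is coded.

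**3. What a shift would do to the test**

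Assume no true effect, 350 patients split 1:1 (175 per arm; the ratio is not stated), two-sided 5%, and wording that lowers Yes answers among controls by Δ. With p₁ the true rate, p₂ = p₁ − Δ and p̄ their mean, the chance of a significant result favouring the video is

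Φ{[Δ − 1.96√(2p̄(1−p̄)/n)] / √[(p₁(1−p₁) + p₂(1−p₂))/n]}.

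For p₁ = 0.30, Δ = 0.10 and n = 175: 1.96√(2 × 0.25 × 0.75/175) = 0.0907, and √[(0.21 + 0.16)/175] = 0.0460. Then (0.10 − 0.0907)/0.0460 = 0.20, and Φ(0.20) = 0.58.

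| n per arm | True rate | Δ = 5, 10, 15 points |
|---|---|---|
| 175 | 30% | 18%, 58%, 92% |
| 175 | 50% | 15%, 47%, 81% |
| 87 (half followed up, assumed) | 30% | 11%, 33%, 66% |
| 87 | 50% | 10%, 26%, 52% |

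These figures show only that a shift of this order would matter. The documents give no basis for choosing Δ.

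**The case against.** The best reply is that Study procedures paraphrases the question and the instrument is S3 Appendix C, which is not shown. Other places fit a common anchor: the Abstract describes the survey neutrally, and follow-up is timed from the initial visit. The section is also loosely drafted. Its next paragraph says that randomized patients who take part receive the video, which cannot literally include controls, so the narrative may simply be told from the viewer's side. This stands as a limit on the claim. A reader might infer that the arms are in fact asked different questions, and the documents do not establish that.

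A reader might also infer that the wording reveals allocation. That does not stand as a separate defect. The trial is openly unblinded, patients know whether they saw a video, and no blinding of callers is claimed. A single script read to everyone would not require the caller to know the arm either.

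Nor do the documents support a definite false benefit for the video of 4 to 12 points. That range needs the assumed rates, and it needs every affected answer to come from an adopter and count as No. The rest of the second table shows smaller, zero or reversed bias.

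Finally, the text says that clinic-visit outcomes are compared between groups, but of follow-up outcomes only that logistic regression is used. Comparison by arm is thus an inference, though a strong one given intention to treat and attrition reported by arm. The outcome is also not the primary one, and lifestyle adoption is not in the article's lists of secondary outcomes.

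**Conclusion.** The point holds as an inconsistency with consequences for a follow-up outcome. As described, the lifestyle-change question does not fit control patients or video-arm patients who declined to watch, and a comparison by randomized arm could pick up the wording in place of an effect. The size and direction are unknown. They depend on how these patients answer and on how Don't Know is coded. The coding may be in an analysis plan that is not shown, and its absence here is not counted as an omission.

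The conclusion assumes that the call goes to both arms, that adoption is compared by arm, and that the article's description matches the questionnaire. If S3 Appendix C already uses a neutral anchor, only a phrase in the article is wrong. The index-visit readiness and confidence scores are untouched. The point ranks below a must-fix but should be settled before calls begin.

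**What to change.** 1. Check S3 Appendix C. If its question is already the same for both arms, correct the phrase in Study procedures and stop there.
2. If not, anchor the question to the index clinic visit for every patient, for example *since your clinic visit on [date]*. The article already times follow-up from that visit.
3. Put any video-specific questions at the end of the call, and ask them only of patients who watched the video.
4. Make Study procedures, the Abstract's description of the survey and S3 Appendix C agree.

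The cost is at most one reworded question, a reordered call script and a minor notification to the review board. Sample size, visits and the primary analysis do not change.
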